## Abstract

**Background:**

Anxiety disorders affect approximately 10% to 20% of young people, can be enduring if left untreated, and have been associated with psychopathology in later life. Despite this, there is a paucity of empirical research to assist clinicians in determining appropriate treatment options. We describe a protocol for a randomized controlled trial in which we will examine the effectiveness of a group-based Acceptance and Commitment Therapy program for children and adolescents with a primary diagnosis of anxiety disorder. For the adolescent participants we will also evaluate the elements of the intervention that act as mechanisms for change.

**Methods/design:**

We will recruit 150 young people (90 children and 60 adolescents) diagnosed with an anxiety disorder and their parent or caregiver. After completion of baseline assessment, participants will be randomized to one of three conditions (Acceptance and Commitment Therapy, Cognitive Behavior Therapy or waitlist control). Those in the Acceptance and Commitment Therapy and Cognitive Behavior Therapy groups will receive 10 × 1.5 hour weekly group-therapy sessions using a manualized treatment program, in accordance with the relevant therapy, to be delivered by psychologists. Controls will receive the Cognitive Behavior Therapy program after 10 weeks waitlisted. Repeated measures will be taken immediately post-therapy and at three months after therapy cessation.

**Discussion:**

To the best of our knowledge, this study will be the largest trial of Acceptance and Commitment Therapy in the treatment of children and young people to date. It will provide comprehensive data on the use of Acceptance and Commitment Therapy for anxiety disorders and will offer evidence for mechanisms involved in the process of change. Furthermore, additional data will be obtained for the use of Cognitive Behavior Therapy in this population and this research will illustrate the comparative effectiveness of these two interventions, which are currently implemented widely in contemporary clinical practice. Anticipated difficulties for the trial are the recruitment and retention of participants, particularly adolescents. To avert these concerns and maximize recruitment, several strategies will be adopted to optimize referral rates as well as reduce participant drop-outs.

**Trial registration:**

This trial is registered with the Australian and New Zealand Clinical Trials Registry, registration number: ACTRN12611001280998

## Background

With a prevalence rate of 10% to 20%, anxiety disorders are the most common mental health concern affecting children and adolescents [1,2]. Young people with anxiety are typically underrepresented in clinical research, and anxiety in children is often minimized by health professionals, potentially due to a common perception that in this population anxiety is developmental, transient and innocuous [3,4]. Despite this, anxiety in childhood increases the likelihood of academic and social skills difficulties as well as substance abuse, and is often enduring if untreated [2]. Furthermore, a childhood history of anxiety is a common precursor to depression, and has been found to predict anxiety and depression in later life [5-7].

In a recent review of the best available evidence for the treatment of psychological disorders, Cognitive Behavior Therapy (CBT) was found to be the first-line evidence-based psychosocial intervention for anxiety among adults and is currently the most empirically supported therapeutic approach for children and adolescents [8]. In part, this is a consequence of insufficient evidence for alternative interventions [8], rather than findings indicating other treatments are unsuitable. Indeed, the dearth of population-specific research in this area is highlighted by the aforementioned review, which found a complete absence of studies assessing the efficacy of CBT in the treatment of panic disorder among children and variable levels of evidence for its use in other anxiety disorders in this population [8]. Furthermore, others have found that one in four children do not benefit from CBT [9]. As such, it is important that other interventions are developed and evaluated to address this shortcoming.

Acceptance and Commitment Therapy (ACT) has sparked increased interest among clinicians and researchers in the last decade [10]. ACT considers the fundamental cause of psychopathology and human suffering to be the interrelationships of cognition, language and life circumstances that lead to decreased capacity to modify or continue exhibiting behaviors that are in the service of personal values [11]. ACT aims to increase psychological flexibility; ‘the process of contacting the present moment fully as a conscious human being and persisting or changing behaviour in the service of chosen values’ [12]. Whereas other therapies focus on altering the content, frequency and form of private experience (thoughts, feelings and sensations), ACT works to modify the function of internal experience - such as supporting individuals to recognize thoughts for what they are, simply thoughts and not necessarily the truth - and thus reduce their bearing on behavior [13]. ACT focuses on assisting clients to live valued meaningful lives [11]. To do this, six core therapeutic processes organized in a ‘hexaflex’ model are employed, including ‘acceptance,’ ‘defusion,’ ‘values,’ ‘committed action,’ ‘the present moment’ and ‘self-as-context’ [14]. These processes are interrelated and support each other in increasing psychological flexibility.

ACT has a growing empirical base demonstrating its efficacy for an array of problems, including the treatment of anxiety concerns among adults such as social phobia [15,16], generalized anxiety disorder [17] and mathematics anxiety [18]. Indeed, in the first known review of published ACT controlled trials up to 2005, the authors found ACT to be superior to control conditions, waitlists and treatment as usual at both post-intervention and at follow-up across a myriad of different problems from psychosis to work stress [12]. Whilst evidence for the use of ACT in adult populations with anxiety has grown, there is currently a paucity of research examining the efficacy of ACT in children and adolescents with anxiety. A literature search produced only one published study, that being a case study [19]. However, preliminary research evidence supports the use of ACT among young people with other problems including depression [20], anorexia [21], chronic pain [22] and high risk sexual behavior [23].

Research evidence has supported the use of mindfulness, one of the ACT core processes, in the treatment of young people. Four studies have assessed the impact of mindfulness-based stress reduction among children and/or adolescents with anxiety and found it to be effective in reducing anxious symptoms [24-27]. A review of these studies has previously been conducted [28]. Although these studies show some early support for the use of ACT for the treatment of childhood problems including anxiety, they are subject to several methodological issues - small samples, a lack of either control group or random assignment, few objective measures, potential biases from recruited volunteers, reliance on self or non-blind parent or teacher reports and employment of non-clinical samples, and/or the inclusion of only one component of the ACT model (that is, mindfulness) - that limit their validity. More rigorous research is required to solidify the effectiveness of mindfulness in the treatment of child anxiety disorders and to extend the research into other ACT core processes.

Clinical research has typically focused on assessing the efficacy of interventions. However, this approach does not assist in the identification of the specific techniques that are empirically effective or, conversely, those that are harmful [14]. Identification of the mechanisms of action within a specific treatment could support clinical practice and enable interventions to be tailored to meet individual client needs. It has been proposed that ACT works by supporting increased acceptance of internal experience and reducing fusion with negative thoughts to enable valued living, referred to in ACT as increasing psychological flexibility [12]. ACT studies have typically focused on evaluation of the core processes of the model, as described above, to examine the validity and impact of each [12]. These studies have found support for the roles of defusion [29] and acceptance [17,30], and some support for the role of values and/or committed action [17] in reducing psychopathology. Ultimately, this emerging research has led to the genesis of three ACT mediational hypotheses, that psychological inflexibility precedes suffering among clinical and non-clinical populations; ACT increases psychological flexibility; and psychological flexibility leads to enhanced well-being, decreased clinical symptoms and increased value-based activities [14]. However, these studies are preliminary and subject to several methodological limitations including measures that lack psychometric evaluation, the use of purely self-report measures and the use of measures that concentrate on a small number of core processes, leaving other parts of the ACT model untested [31]. Thus, to build upon the current empirical literature in this area, this randomized controlled trial design includes the investigation of mechanisms of change in adolescents with anxiety.

In summary, preliminary investigations of ACT in the treatment of adult anxiety have produced promising results. Other studies have also supported the use of mindfulness - one of the six ACT core processes - in the treatment of childhood anxiety, which suggest that approaches employed within ACT appear to be suitable for child populations. To the best of our knowledge, this will be the first randomized controlled trial to examine the effectiveness of ACT in young people with a diagnosed anxiety disorder. Given the popularity and use of ACT in clinical practice [10], it is imperative that this form of intervention be empirically evaluated for its efficacy. Thus, the aim of this research is to examine the effectiveness of a manualized ACT group-therapy program in the treatment of anxiety disorders among children and adolescents. It is hypothesized that ACT will be at least as effective in the treatment of anxiety disorders in these populations relative to a manualized CBT group-therapy program, and that ACT will be more effective in the treatment of anxiety disorders in this population relative to the control condition at both immediate post-treatment and at three-month follow-up on outcome measures. The secondary aim of the trial concerns the adolescent participants and is to identify the mechanisms of change surrounding the intervention that are critical to changes in outcome measures. It is hypothesized that these will include decreased experiential avoidance and cognitive fusion, as well as increased emotional awareness, acceptance and valued living.

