## Methods

### Study design

This is a prospective randomized controlled trial. It is a three (group: two intervention and one control) by three (time: pre-, immediate post- and three-month post-treatment) repeated measures factorial design. The overall study design is illustrated in Figure 1.

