#### Follow-up assessment

Follow-up repeated measures assessment will be completed immediately post-treatment - or after 10 weeks for the control group - and three months post-treatment for both intervention groups. Following completion of the 10-week post assessment, the control group will complete a program of 10 × 1.5 hour sessions of CBT. Although it will not be possible to ensure the researchers conducting post-intervention and follow-up assessments will be blinded to the treatment type, to reduce potential bias these interviews will be recorded for reliability purposes and reviewed and re-rated by an independent assessor - a psychologist within the Department of Psychological Medicine with training in the use of the ADIS-IV - blind to the diagnosis obtained. Participants will also be assessed on the uptake of pharmacotherapy throughout the course of the trial at follow-up.

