### Controls

The control group in the study will be a waitlist group, also diagnosed with an anxiety disorder. Participants allocated to this group will complete baseline assessments and will receive CBT following a waiting list period of 10 weeks. This period was selected as it corresponds with the 10 week program, allowing for comparative post measure. It was considered unethical to withhold treatment for longer than 10 weeks.

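### Superiority of ACT over the waitlist at three-month follow-up cannot be tested: by then the waitlist has moved to CBT and has no scheduled assessment

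*Protocol article*

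**What the plan says.** The Background sets out the primary aim as two comparisons: ACT at least as effective as CBT, and ACT more effective "relative to the control condition at both immediate post-treatment and at three-month follow-up on outcome measures". Only the mechanism question is called secondary.

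Study design makes the matching structural statement: "It is a three (group: two intervention and one control) by three (time: pre-, immediate post- and three-month post-treatment) repeated measures factorial design".

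The Follow-up assessment section gives the visit schedule. Assessments take place "immediately post-treatment - or after 10 weeks for the control group - and three months post-treatment for both intervention groups". It continues: "Following completion of the 10-week post assessment, the control group will complete a program of 10 × 1.5 hour sessions of CBT".

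The Controls section repeats that participants in this arm "will receive CBT following a waiting list period of 10 weeks". It explains that the length was matched to the treatment program so that a post-treatment comparison could be made, and adds: "It was considered unethical to withhold treatment for longer than 10 weeks". The Abstract also states the crossover.

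**The concern.** The hypothesis and the design statement both require an untreated control group observed at three months. The schedule provides neither the untreated state nor the observation. If the text stands, a stated part of the primary aim has no comparator.

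The risk lies in what might fill the gap. A three-month result labelled ACT versus control could come only from week-10 waitlist values carried forward, from model extrapolation, or from controls who have since received CBT. None of these is a randomized comparison of ACT with no treatment at that time, yet a reader could take the result as evidence of durable superiority.

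**Working it through.** The plan states no figure to reproduce here, and the point does not depend on sample size, power or significance level. The check sets the sections side by side and works out the timeline.

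**Step 1: which cells the schedule fills** (Study design against Follow-up assessment)

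| Group | Baseline | Post-treatment / week 10 | Three months post-treatment |
|---|---|---|---|
| ACT | yes | yes | yes |
| CBT | yes | yes | yes |
| Waitlist | yes | yes | none scheduled; CBT has been given |

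The design statement implies 3 × 3 = 9 cells. The schedule yields 9 − 1 = 8.

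**Step 2: timeline in weeks**

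Inputs: 10 weekly sessions (Abstract, Intervention); a 10-week wait and then 10 sessions of CBT (Follow-up assessment, Controls). Assumptions: treatment and waiting start together at week 0, waitlist CBT starts at once and runs weekly, and three months is 12 to 13 weeks.

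- ACT and CBT arms finish treatment: week 10.
- Their three-month visit: 10 + 12 = 22 to 10 + 13 = 23.
- Waitlist CBT: starts at week 10 and ends at 10 + 10 = 20.
- Gap between the end of waitlist CBT and that visit: 22 − 20 = 2 to 23 − 20 = 3 weeks.
- If controls were instead assessed three months after their own CBT: 20 + 12 = 32 to 20 + 13 = 33.

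Under either timing, the control data would come after a full CBT course.

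**Step 3: which hypothesized contrasts survive**

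Reading the time phrase as covering both comparisons gives 2 comparisons × 2 times = 4 contrasts.

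- ACT versus CBT, post-treatment: testable.
- ACT versus CBT, three months: testable.
- ACT versus waitlist, week 10: testable.
- ACT versus waitlist, three months: not testable.

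The loss is 1 of 4 contrasts overall, and 1 of the 2 that involve the control.

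**Step 4: whether the planned analysis can recover it**

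Statistical analysis names linear mixed models and full information maximum likelihood. These methods recover information on missing outcomes from participants who were observed. Here the untreated three-month outcome is unobserved for every control. With categorical time, a full 3 × 3 model has (3 − 1) × (3 − 1) = 4 interaction degrees of freedom. Eight cell means support 8 − 1 − 2 − 2 = 3. The missing one is the one that the control contrast at three months needs. A model that returns a value for it does so through an assumption about the untreated course after week 10, which the data cannot check.

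**The case against.** The strongest reply is that the operational plan is sound and open. The crossover is stated in the Abstract, Follow-up assessment and Controls, and the Controls section says that the wait was chosen for the post-treatment comparison. Sample size calculation and Statistical analysis both speak of pre-versus-post comparisons, and nowhere is a three-month ACT-versus-waitlist test specified. Nothing says that week-10 values will be carried forward or that post-CBT data will be used. On this view the fault is over-broad wording in one Background sentence and one design label, and three of the four contrasts are unaffected.

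Much of this stands. The schedule is coherent, the other contrasts are intact, and which workaround the analysts would choose is unknown, so a misleading result is a risk and not a stated plan. The week numbers are also approximate, because groups have to be filled and no start dates are given.

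It can also be argued that controls may have a three-month visit after all. The inclusion criteria ask every participant to be available for one, the Abstract describes three-month measures in general terms, and the design figure is not available to this review. The specific schedule in Follow-up assessment points the other way. Even if such a visit exists, the crossover is stated in the text, so no figure or analysis plan can make those data untreated.

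The objection does not remove the conflict. The time phrase, however it is read, includes the control at three months, and Study design says the same.

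**Conclusion.** The concern holds. The Background hypothesis and the Study design statement claim a comparison that the Follow-up assessment and Controls sections rule out. There are two separate reasons: no three-month assessment is scheduled for controls, and controls have been moved to CBT by then. The second is sufficient alone and is the more secure, since it is stated in three places; the first rests on one clause in Follow-up assessment.

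The scope is one of the two time points of the ACT-versus-control hypothesis, with no untreated control participants at that time. The timeline of about week 22 to 23 against about week 20 assumes prompt starts, but the conclusion needs only that controls begin CBT after week 10 and before the three-month visit. Because a stated part of the primary aim cannot be tested as written, it has to be corrected, although the correction is small.

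**What to change.** 1. In the Background, limit ACT versus waitlist to the immediate post-treatment (10-week) assessment, and apply the same limit to any CBT-versus-waitlist comparison.
2. Restrict the three-month hypothesis to ACT versus CBT. Report maintenance within each arm as description only.
3. In Study design, replace the three-by-three factorial with three arms at two time points plus a two-arm three-month follow-up. Make the general statements about three-month assessment in the Abstract and the inclusion criteria agree with the schedule in Follow-up assessment.
4. In Statistical analysis, state that waitlist data collected after CBT starts never enter a control contrast.

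The cost is rewording of the hypothesis, design and analysis sections, and giving up the claim of superiority over control at three months, which the design cannot support. Arms, treatment schedule and sample size are unchanged, as are the visits set out in Follow-up assessment. The trial is listed as recruiting, so the change can be recorded as an amendment.

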## Methods

### Study design

This is a prospective randomized controlled trial. It is a three (group: two intervention and one control) by three (time: pre-, immediate post- and three-month post-treatment) repeated measures factorial design. The overall study design is illustrated in Figure 1.

**Figure 1 F1:**
[figure not shown]
Study design.

### Participants

Participants will be approximately 150 children (90 younger and 60 older children) aged 7 to 17 years with a primary diagnosis of a Diagnostic and Statistical Manual of Mental Disorders (DSM-IV) anxiety disorder. The participants will be age-classified as ‘children’, aged 7 to 11 years, and ‘adolescents’, aged 12 to 17 years. Twelve years of age was determined as the cut-off point to be consistent with other research involving ACT as a treatment for problems among adolescents [20].

Participants will be recruited via referrals to the Department of Psychological Medicine, The Children’s Hospital at Westmead (CHW), Sydney, NSW, Australia. Referrals will be accepted from anyone, including health professionals (general practitioners, psychologists, pediatricians), educational providers, and self-referrals. Written informed consent will be obtained from the parent or caregiver of the children and from the child/adolescent. Ethical approval was obtained for this study from the Human Research Ethics Committee at CHW and at The University of Newcastle.

The researchers predict that the majority of referrals will come from school counselors, followed by word of mouth, then via parents’ referral through the CHW intake phone line. In terms of proportions, it is expected that 60% to 70% of referrals will come from school counselors. On the basis of recruitment efforts to date and requests to intake phone line, the researchers consider that the anticipated sample will be achieved.

### Inclusion criteria

1. Aged between 7 and 17 years

2. Criteria met for a primary diagnosis of a DSM-IV anxiety disorder (including panic disorder and/or agoraphobia, obsessive compulsive disorder, specific phobia, social anxiety disorder or generalized anxiety disorder)

3. Available and able to attend CHW for pre-treatment, immediate post-treatment and three-month post-treatment assessments as well as attending a minimum of 80% of therapy sessions

4. Have a parent or caregiver who is willing to attend and participate in the assessment as well as a minimum of 80% of therapy sessions.

### Exclusion criteria

1. Developmental or language delay, as reported by the parent or caregiver

2. Non-English speaker

3. Complex mental health problems such as psychosis, conduct disorder or active suicidality

4. Complex medical conditions with a high degree of medical dependence that would prevent them from being able to attend at least 80% of sessions

5. Attention deficit disorder with hyperactivity (ADHD) that is not well controlled. In addition to initial screening via parent and teacher reports as well as by a physician, as appropriate, ADHD will be assessed by clinicians according to DSM-IV criteria during the initial assessment. It was determined that, unless ADHD is sufficiently controlled, the group-based 1.5 hour program is an unsuitable structure for both the child with this identified concern as well as other group members

6. Medicated with an anxiolytic or antidepressant for less than two months. However, in the instance of a participant experiencing a marked increase in symptom severity across treatment, there may be a need to consider pharmacotherapy. Participants will have weekly contact with the researchers across the course of the program and changes in functioning or status will be monitored in an ongoing way. Where a participant’s progress appears to be worsening, a case-by-case consideration of the need for a medical assessment for potential commencement of pharmacotherapy will be undertaken. In addition to this, the uptake of medication external to that identified across the trial will also be assessed at follow-up assessment. If a participant does utilize medication of this kind throughout the course of the study, they will be excluded from data analysis.

7. Post-traumatic stress disorder (due to the potential distress caused to other participants in the group and the specialized treatment required for this disorder)

8. Completed <70% of sessions or dropped out of treatment - those who become lost to follow-up will be placed in the intention-to-treat category.

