#### Randomization

Following baseline assessment, eligible participants and their caregivers will be randomized to one of three conditions - ACT, CBT or a waitlist control group - for a period of 10 weeks (described in detail below). Each group will comprise up to eight children/adolescents as well as their caregivers. The researchers involved in this study are six registered psychologists, all trained in ACT and CBT. This will be a block randomized controlled trial, with the participant serving as the unit of randomization. Randomization will be undertaken via a publically available random assignment software application, ‘Graphpad’ [http://www.graphpad.com/quickcalcs/].

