### Statistical analysis

Data coding and analysis will be conducted using the IBM SPSS Statistics v.21 software program. Primary outcome measures will be examined both with intention-to-treat analyses and analyses conducted on treatment completers. For the efficacy hypotheses, paired t-tests and linear mixed models will be used to investigate changes in pre versus post primary and secondary outcome measures. Statistical significance will be considered as *P <*0.05. The mixed model approach has been selected as it allows for inter-participant and intra-participant variance as well as the inclusion of participants with missing data, whilst maintaining power.

In accordance with the protocol of Forman *et al*. [70], mechanism of change hypotheses will be examined using correlation and independent t-tests to determine which variables to include in a multivariate analysis of variance. Post-hoc multiple comparisons (for example, Bonferroni correction) will be performed to determine where significant differences lie. Multivariate regression examining factors related to treatment success will also be employed and will include examining any demographic (such as age, gender, family functioning) and clinical (such as pre-scores, psychological flexibility) factors that might be related to outcomes. Mediational analysis, a regression-based approach, will be used to test hypotheses about the mechanisms behind outcome, as this is a powerful way of determining mechanisms by which an effect operates rather than the existence of an effect [73]. It allows for more than one mediator and adjusts all paths for the potential influence of covariates not proposed to be mediators in the model. Receiver operating curve plots of the true positive and false positive rate for different possible cut-points of the regression test will be conducted because receiver operating curves convey information relating to the trade-off between sensitivity and specificity, and maximize predictive value. The coordinates of the receiver operating curve will be used to determine the optimal cut-point for the test. The full information maximum likelihood method will be used to deal with missing data.

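### Dropping randomized participants who take up medication contradicts the planned intention-to-treat analysis, and the analysis status of low attenders is left unclear

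*Protocol article*

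**What the plan says.** Under Randomization, allocation comes after eligibility has been settled: "Following baseline assessment, eligible participants and their caregivers will be randomized to one of three conditions".

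Item 6 of the Exclusion criteria opens with a baseline condition, namely having taken an anxiolytic or antidepressant for under two months. It then turns to events during treatment, in a sentence that begins: "Where a participant’s progress appears to be worsening, a case-by-case consideration of the need for a medical assessment for potential commencement of pharmacotherapy will be". It closes with "If a participant does utilize medication of this kind throughout the course of the study, they will be excluded from data analysis". The Follow-up assessment section shows when this is known: "Participants will also be assessed on the uptake of pharmacotherapy throughout the course of the trial at follow-up".

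Item 8 of the same list reads: "Completed <70% of sessions or dropped out of treatment - those who become lost to follow-up will be placed in the intention-to-treat category".

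The Statistical analysis section says: "Primary outcome measures will be examined both with intention-to-treat analyses and analyses conducted on treatment completers". It chooses the mixed model because it allows for variation between and within participants, "as well as the inclusion of participants with missing data, whilst maintaining power", and it names full information maximum likelihood for missing data.

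**The concern.** Medication uptake and session attendance can be known only after randomization, so neither can be an entry criterion. The medication sentence matters more. It sets no limit to a completer set, so on its face it applies to every analysis, including intention-to-treat. It is also tied to the outcome: by item 6's own account, medication comes into question when a participant is getting worse, so those removed are likely to be treatment failures. If the arms lose different shares of their failures, the comparison is no longer the randomized one.

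**Working it through.** **No plan figure to reproduce.** The article gives no rate of medication uptake or low attendance. Its one design figure, 30 per group at power 0.8 and effect size 0.6 to 0.7, is not used below. For the record, a one-sided two-sample calculation at 0.65 gives 30; a two-sided one gives 44 at 0.6 and 33 at 0.7.

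**Can both instructions be followed?** Statistical analysis plans intention-to-treat for the primary outcomes. Item 6 removes medication users from data analysis, and no section confines that to completers. With one or more users, no planned analysis contains everyone randomized.

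**Do the missing-data methods repair this?** No. The mixed model and full information maximum likelihood deal with missing values in participants who stay in the dataset. A participant who is removed contributes nothing, not even a baseline.

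**Could removal differ by arm?** Yes, in either direction.
- Untreated waitlist participants might worsen more and so take up medication more often. This is an assumption.
- Item 6's weekly contact runs over the program, and the waitlist has no program in its first 10 weeks (Controls). The three-month assessment is specified for the two intervention groups (Follow-up assessment). Uptake could therefore be detected more often in ACT and CBT.
- As worded, a participant who starts medication after week 10 also drops out of the week-10 comparison.

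**Size, first model.** Assume the worst share q of an arm is removed, on a trigger whose correlation with the outcome is ρ. The arm's mean then improves by ρ × φ(z) / (1 − q), where z is the normal quantile at 1 − q and φ the normal density. At ρ = 1:
- q = 0.05: 0.1031 / 0.95 = 0.109
- q = 0.10: 0.1755 / 0.90 = 0.195
- q = 0.15: 0.2332 / 0.85 = 0.274
- q = 0.20: 0.2800 / 0.80 = 0.350

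The loss in the ACT–waitlist difference (SD) is the waitlist value minus the ACT value:

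| Removed, waitlist / ACT | ρ = 0.3 | ρ = 0.5 | ρ = 1 |
|---|---|---|---|
| 10% / 10% | 0.00 | 0.00 | 0.00 |
| 10% / 5% | 0.03 | 0.04 | 0.09 |
| 15% / 5% | 0.05 | 0.08 | 0.17 |
| 20% / 5% | 0.07 | 0.12 | 0.24 |

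Swapping the arms gives the same values with the opposite sign.

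**Size, second model.** Assume those removed score 1 SD worse than their arm's mean. The arm's mean then improves by q / (1 − q). From a true difference of 0.60 SD:
- 15% / 5%: 0.60 − (0.176 − 0.053) = 0.48
- 20% / 5%: 0.60 − (0.250 − 0.053) = 0.40

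**Sample lost.** Assume equal allocation, 150 / 3 = 50 per arm. Approximate two-sided power at 0.6 SD is Φ(0.6 × √(n/2) − 1.96): 0.85 at n = 50, 0.83 at 47.5 (5% removed from each arm) and 0.77 at 40 (20% removed from each arm).

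**Item 8.** It sits in the exclusion list but expressly assigns only those lost to follow-up to intention-to-treat. Someone who attended under 70% of sessions, or stopped treatment, and was still assessed has no stated place. Waitlist participants have no sessions before week 10, so the rule cannot apply to them in that comparison. If it were used as an exclusion, it would filter the active arms only.

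**The case against.** The strongest defense is that the article plans intention-to-treat and completer analyses side by side, and that items 6 and 8 are completer rules put in the wrong list. For item 8 this largely stands. The item mentions intention-to-treat, and under 70% attendance reads naturally as a clumsy definition of a non-completer. A reader might infer that low attenders are removed from the intention-to-treat analysis, but the text does not establish that; it leaves the matter open. For item 6 the defense fails, because the sentence has no such limit.

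A second objection is that bias requires removal or selection to differ between arms. That is correct. A reader might infer that every between-arm comparison is biased, but the documents do not show it: equal uptake with the same selection gives no shift. For ACT against CBT, both rules apply to both arms alike. Nor do the documents support presenting the rule as reliably conservative, since its direction is unknown.

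A reader might also see a conflict between 70% here and the Inclusion criteria's 80%, where item 3 includes "as well as attending a minimum of 80% of therapy sessions". That item opens with availability and ability to attend, and item 4 concerns a caregiver's willingness. The 80% is thus an expectation at entry, while the 70% concerns sessions actually completed. They measure different things and do not contradict each other.

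Finally, both models assume uptake rates, and the second fixes a 1 SD deficit and ignores any benefit from the medication. This is why the sizes are only illustrative.

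**Conclusion.** The last sentence of item 6 contradicts the planned intention-to-treat analysis and puts the between-arm comparisons at risk of bias. This follows from the wording and needs no assumed figure. Direction and size are unknown. On assumed rates the ACT–waitlist shift runs from 0 SD, with equal uptake and the same selection, to about 0.2 SD, with 15% to 20% against 5% removed and strong selection (0.17 to 0.24 SD in the first model, 0.12 to 0.20 in the second). With weak to moderate selection at those rates it is 0.05 to 0.12 SD. It would reverse if uptake were higher, or detected more often, in the active arms. Against a planned effect of 0.6 to 0.7, the larger values matter.

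Item 8 is an ambiguity to resolve, not a demonstrated removal from intention-to-treat. The need to correct the plan before the data are analyzed rests on the medication sentence alone.

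**What to change.** - Leave the baseline medication criterion in item 6 as an eligibility rule, and delete the item's last sentence.
- Define the intention-to-treat set as all randomized participants in their allocated arm, whatever their medication uptake or attendance, with outcomes sought for all of them.
- Move item 8 out of the exclusion list and use it only to define the secondary completer analysis.
- Report medication uptake by arm, and run one sensitivity analysis that omits data after medication starts or otherwise handles them by a stated rule.

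The cost is protocol wording and one extra analysis. Uptake is already to be assessed, though its start date must be recorded if data after that date are to be omitted. The downside is that the intention-to-treat estimate will include any effect of medication, which the uptake table and sensitivity analysis help the reader to judge. Clinical management does not change.
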